### Data collection

Data will be collected from November 2011 to June 2013. The study will have a total length of 30 months, but time monitoring of each patient will last 12 months. The recruitment period will be 18 months, and patients will be evaluated during 12 months, starting from the date of their recruitment. Once the enrolment period ends, the final 12 months will be only used to evaluate the latest patients. However, for ethical considerations, all patients will be followed periodically by phone calls and further medical history review in the routine control appointment with the physician. Monitoring and evaluation of the variables related to the study (including questionnaires) will take place as follows: at baseline, which corresponds to the day of study entry, and every 3 months at the patients’ check-ups to complete the year of follow-up. The data obtained in this study will be registered in an electronic database that will include the Morinsky-Green questionnaire to measure medication adherence, the scale SF-36 Health Status Questionnaire to estimate quality of life, the Clinical Global Impression for Bipolar Modified (CGI-BP-M) scale to measure the assessing global of illness, the Young Mania Rating Scale for evaluating mania, and the Hamilton Depression Rating Scale to measure depression. Data regarding medication history, interviews with the pharmacist, health current status, plans of action will be registered as well. Related to the primary outcome, in addition to the information provided by patients and family members, the pharmacist gets the information from the records of medical history of the patients, provided by SJDC.

### Data management

Data will be stored in a database Microsoft Access, 2007 with all patients’ information: details of medications and treatments, physical assessment records, laboratory tests, hospitalizations, and appointments. The database has an application that allows the use of psychiatric rating scales, and that information will also be incorporated in the database. The database shows reports of a patient’s assessment forms, monitor of the identified problems, and generates reports according to the user’s needs. The participant’s files and knowledge questionnaires are strictly confidential and will be archived in SJDC. Researchers involved in this study would be the only ones with access to the information. The pharmacist will perform a complete data backup every day, and the information will be stored in two different hard drives as a safety measure.

### Ethical issues

Institutional review boards that approved the study were: Faculty of Pharmaceutical Chemistry’s Research Technical Committee at Universidad de Antioquia, the SJDC’s Bioethics Committee (Reference Number: 06/10) and two healthcare providers’ Bioethics Committee: COOMEVA (Reference Number: 15/11) and SURA (Reference Number: 3/11). Each patient will receive verbal and written information about the study (purpose, procedures, potential risks, benefits, and information confidentiality), and also a copy of the informed consent form, which explains the study in detail. Once the patients resolve any doubts about the study, those who agree to participate must sign the informed consent form. The pharmacist must keep the original form and give a copy to the patient. The patient’s personal information (name, identification, address, age, gender, marital status, education, co-morbidities, prescription drugs) will never be disclosed at any phase of the clinical trial (final results, publications, or project presentations). The authors will guarantee publication of the outcomes of the clinical trial, and the results will be disseminated among the participants. A clinical monitor of the study will be reviewing the process constantly.

### Sample size calculation

The sample size and power were calculated using EpiInfo™ version 6.04 (Centers for Disease Control and Prevention, Atlanta, GA, USA). Assuming readmissions will be 50% in the control group and 30% in the intervention group, with a confidence of 95% and a power of 80%, it would be required to include at least 166 patients. The estimated sample size of 200 patients with a BD-I diagnosis is needed to cover losses during the follow-up and to increase sensitivity towards secondary objectives.

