### Randomization

Patients will be assigned to the intervention or the control group through a computer-generated randomization - designed by a person external to the study and otherwise unrelated to it - using Microsoft ® Excel 2007. Participants will be assigned to the treatment groups in sequential order, and the randomization list will be strictly confidential (randomization list maintained off-site by the study coordinator, only one person outside the study knows it). The software generates a sequence of 500 random numbers without repetition (1 to 500), assigning a control group code to 250 numbers and an intervention group code to the other 250. Subsequently, the numbers generated are automatically sorted in ascending order to determine each patient’s allocation to one of the two study groups. Participants will be assigned to the intervention or the control group in sequential order once the study’s coordinator (the pharmacist) verifies fulfillment of inclusion criteria.

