### Biostatistical considerations

Data will be analyzed according to the intention-to-treat principle. All patients will be analyzing according to their allocated treatment group. Statistical analysis will be blinded and performed using SPSS version 13.0 (IBM SPSS, Armonk, NY, USA). Control and intervention groups will be compared in terms of the proportion of changes from baseline to 12 months following. Repeated-measures analysis will carry out. Clinical assessments will be made at baseline and every 3 months during the study period. Follow-up will be continuing to complete the year, even if a relapse or psychiatric hospitalization occurred. The main end points of interest are the number and duration relapse events per person-year of follow-up and number of admissions to the hospital due to BD. Data will be reported as means and standard deviations (SD) or as percentages. The Pearson chi-square test (between study groups) and the McNemar test (within-group changes from baseline to follow-up at 12 months) will be used to compare proportions. Comparisons for categorical variables will be conducted by using Chi-square tests (the Fisher exact test when appropriate) and for continuous variables by using the independent-sample t test (Mann-Whitney U test when appropriate). The Mann-Whitney test will be used to compare outcomes between groups. For quality-of-life questionnaire the Student’s t test will be used if sample distribution proves to be normal. Otherwise, the Wilcoxon rank-sum test will be used. The paired Student’s t-test (within-group changes from baseline to follow-up at 12 months) or the independent sample Student’s t-test (between study groups) will be used to compare means; odds ratios (ORs) and 95% confidence intervals (CIs) will be estimated as well. Mean number and duration of relapse events normalized to person-time, will be compared between groups using the Student’s t test. Multivariable analyses will be performed to explain the association of multiple variables associated with the factors significantly related to primary outcome: hospitalizations, readmission, relapse and total number of episodes of illness, number and total days of hospitalizations, days of illness, and days of free intervals per year. The sociodemographic and clinical variables to assess will be: duration previous episodes, severity of depression or mania, polarity of the last episode (manic, hypomanic, depressive, or mixed), co-morbid psychiatric illness, social support, psychosocial factors, educational level, living in rural area, having a history of violence to others, having no insight, non-compliance to medication, lack of practical support from the family. Analysis of depression and mania episodes, adherence to pharmacotherapy and quality of life will be performed, using repeated measure analysis. Comparisons will be analyzed using two-tailed tests, *P* <0.05 will be considered as statistically significant.

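### The minimum of 166 patients does not give 80% power for 50% vs 30%; the plan's own inputs require 186, and 166 gives about 75%

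*Protocol article*

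**What the plan says.** Under Sample size calculation, the protocol article sets the effect: "Assuming readmissions will be 50% in the control group and 30% in the intervention group". It names EpiInfo 6.04 as the software and concludes that "with a confidence of 95% and a power of 80%, it would be required to include at least 166 patients". It then moves from that minimum to the recruitment target: "The estimated sample size of 200 patients with a BD-I diagnosis is needed to cover losses during the follow-up", with added sensitivity for the secondary objectives as a second reason. No loss rate is given.

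Two other sections fix the remaining inputs. Biostatistical considerations states that "Comparisons will be analyzed using two-tailed tests", with significance at P below 0.05, and plans the Pearson chi-square test for proportions between groups. Randomization describes a list of 500 numbers, "assigning a control group code to 250 numbers and an intervention group code to the other 250", which is 1:1 allocation.

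**The concern.** Everything needed to recompute the minimum is printed: both event rates, the confidence level, the power, the number of tails, the allocation and the test. The result does not follow from them. A 20-point difference around an average of 40% needs more than 83 patients per arm for 80% power at two-sided 5%.

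The figure of 166 is the only quantitative basis given for the sample size, and 200 is presented as that minimum plus an allowance. If the minimum is too low, the stated power is not delivered there, and the allowance for loss is smaller than a reader would take it to be. Follow-up lasts 12 months and the article lists five reasons for withdrawal or termination, so the size of that allowance matters.

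**Working it through.** **Inputs**

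- Control rate p1 = 0.50 and intervention rate p2 = 0.30 (Sample size calculation). Difference d = 0.20, mean rate 0.40.
- 95% confidence and two-tailed tests (Sample size calculation; Biostatistical considerations): z = 1.960.
- Power 80% (Sample size calculation): z = 0.8416.
- Allocation 1:1 (Randomization).
- Pearson chi-square test, no continuity correction mentioned (Biostatistical considerations).

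**Attempt to reproduce 166**

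Standard two-proportion formula, per arm:

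n = [z(alpha) × √(2 × 0.40 × 0.60) + z(power) × √(0.50 × 0.50 + 0.30 × 0.70)]² / d²

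= [1.960 × √0.48 + 0.8416 × √0.46]² / 0.04

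= [1.3579 + 0.5708]² / 0.04 = 92.999, so 93 per arm and **186** in total.

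With continuity correction:

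n' = (n/4) × [1 + √(1 + 4/(n × d))]² = (92.999/4) × [1 + √(1 + 4/18.6)]² = 102.76, so 103 per arm and **206** in total.

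Other formulas with the same inputs:

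| Variant (two-sided 5%, 80% power) | Total |
|---|---|
| Unpooled variance, 1:1 | 182 |
| Pooled variance in both terms, 1:1 | 190 |
| Arcsine, 1:1 | 186 |
| Unequal allocation (1:2, 2:1, 1:3) | 207 or more |

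The smallest of these, 182, is still 16 patients above 166. Choice of formula and rounding do not explain the gap.

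**Settings that do give 166**

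- One-sided 5% (equivalent to 90% two-sided confidence), 80% power, continuity-corrected: 82.84 per arm, so 83 and 166 in total.
- Two-sided 5%, 75% power, uncorrected: 82.39 per arm, so 83 and 166 in total.

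The first conflicts with the 95% confidence and the two-tailed rule, the second with the stated 80% power.

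**Power at given numbers of patients with outcome**

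Power = Φ{[d × √n − 1.960 × √0.48] / √0.46}, with n per arm. For n = 83: [1.8221 − 1.3579] / 0.6782 = 0.684, and Φ(0.684) = 0.753.

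| Total | Per arm | Power, formula | Power, exact Pearson | Power, continuity-corrected |
|---|---|---|---|---|
| 166 | 83 | 75.3% | 75.1% | 69.9% |
| 186 | 93 | 80.0% | 79.9% | 75.5% |
| 200 | 100 | 82.8% | 83.2% | 78.8% |

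At 180 with outcome (90 per arm, 10% loss, an illustrative rate), the formula gives [1.8974 − 1.3579] / 0.6782 = 0.795, a power of 78.7%.

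**Margin for loss in 200**

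- From 166: (200 − 166)/200 = 17%.
- From 186: (200 − 186)/200 = 7%.
- From 206: none; 200 is 6 short.

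**The case against.** The best defence is that 166 is only an intermediate figure. The trial recruits 200, and 200 gives 82.8% power for the planned Pearson test, above the stated 80%. Even at 10% loss the power is within about 1.3 points of target. That stands: the trial as recruited is not grossly underpowered, and no design decision depends on the correction.

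Second, the 17% margin is derived from 166/200. The article states no loss rate, never says that 80% power survives 17% loss, and gives a second reason for the extra patients. That also stands, so the 17% is what a reader would infer and not a claim of the plan.

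Third, the 7% treats each lost patient as contributing nothing. The plan keeps all randomised patients, imputes missing values, and takes hospitalisations partly from clinic records. Deletion is therefore a simple approximation, although imputation does not restore the information in an outcome that was never observed.

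Fourth, no continuity correction is planned, so 186 is the figure that matches the test and 206 matters only if the correction was intended.

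Finally, the calculation concerns a yes/no readmission outcome, whereas the primary outcomes are three counts. Any corrected power statement should be labelled accordingly. None of this makes 166 follow from the printed inputs.

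**Conclusion.** The stated minimum is wrong for the stated inputs. At two-sided 5%, 80% power and 1:1 allocation, 50% vs 30% needs 186 patients, 20 more than printed, or 206 with a continuity correction. At 166 the power is about 75%, five points below the claim. Because the article prints all the inputs and the result, an analysis plan not shown here could not reconcile them.

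The practical effect is on the margin for loss. Under the planned test, 200 patients keep 80% power down to 186 with outcome (7% loss) and have about 75% at 166. These loss figures rest on counting a lost patient as no information, and all power figures refer to the comparison of readmission proportions. Which setting produced 166 cannot be told from the article; the two that match are an inference.

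**What to change.** In Sample size calculation, replace 166 by 186, the figure for the planned uncorrected Pearson test. If a continuity-corrected calculation was intended, give 206, say so, and acknowledge that 200 then yields 78.8% even without loss. If a one-sided or 90% setting was entered, disclose it and reconcile it with the two-tailed rule in Biostatistical considerations.

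Add a sentence stating that, for the comparison of readmission proportions, 200 patients give 83% power with no loss, 80% with 186 outcomes observed (7% loss) and 75% with 166. State the loss rate expected, and do not let the text suggest that 200 covers 17% loss at 80% power.

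The cost is one paragraph of wording and a slightly less favourable statement of power under loss. With the uncorrected test, no additional patients are needed for the stated power at 200 without loss.

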### Biostatistical considerations

Data will be analyzed according to the intention-to-treat principle. All patients will be analyzing according to their allocated treatment group. Statistical analysis will be blinded and performed using SPSS version 13.0 (IBM SPSS, Armonk, NY, USA). Control and intervention groups will be compared in terms of the proportion of changes from baseline to 12 months following. Repeated-measures analysis will carry out. Clinical assessments will be made at baseline and every 3 months during the study period. Follow-up will be continuing to complete the year, even if a relapse or psychiatric hospitalization occurred. The main end points of interest are the number and duration relapse events per person-year of follow-up and number of admissions to the hospital due to BD. Data will be reported as means and standard deviations (SD) or as percentages. The Pearson chi-square test (between study groups) and the McNemar test (within-group changes from baseline to follow-up at 12 months) will be used to compare proportions. Comparisons for categorical variables will be conducted by using Chi-square tests (the Fisher exact test when appropriate) and for continuous variables by using the independent-sample t test (Mann-Whitney U test when appropriate). The Mann-Whitney test will be used to compare outcomes between groups. For quality-of-life questionnaire the Student’s t test will be used if sample distribution proves to be normal. Otherwise, the Wilcoxon rank-sum test will be used. The paired Student’s t-test (within-group changes from baseline to follow-up at 12 months) or the independent sample Student’s t-test (between study groups) will be used to compare means; odds ratios (ORs) and 95% confidence intervals (CIs) will be estimated as well. Mean number and duration of relapse events normalized to person-time, will be compared between groups using the Student’s t test. Multivariable analyses will be performed to explain the association of multiple variables associated with the factors significantly related to primary outcome: hospitalizations, readmission, relapse and total number of episodes of illness, number and total days of hospitalizations, days of illness, and days of free intervals per year. The sociodemographic and clinical variables to assess will be: duration previous episodes, severity of depression or mania, polarity of the last episode (manic, hypomanic, depressive, or mixed), co-morbid psychiatric illness, social support, psychosocial factors, educational level, living in rural area, having a history of violence to others, having no insight, non-compliance to medication, lack of practical support from the family. Analysis of depression and mania episodes, adherence to pharmacotherapy and quality of life will be performed, using repeated measure analysis. Comparisons will be analyzed using two-tailed tests, *P* <0.05 will be considered as statistically significant.

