### Study outcomes

#### *Evaluation/assessment variables/measuring instruments*

The primary outcomes to be measured are: (1) the number of hospitalizations; (2) the number of emergency service consultations; and (3) the number of unscheduled outpatient visits. In addition to the information provided by patients and family members about the primary objective, the pharmacist gets the information from the records of medical history of the patients, provided by SJDC.

The secondary outcomes to be measured are: (1) adherence to treatment through serum lithium levels, serum valproate levels, carbamazepine-serum levels, and by the questionnaire of Morinsky-Green (MG) [21]; (2) life quality through the Quality of Life Scale: The Short Form (36) Health Survey Questionnaire [22]; (3) Clinical Global Impression for Bipolar Modified scale, CGI-BP-M [23]; (4) Young Mania Rating Scale for the evaluation of mania [24]; (5) Hamilton Rating Scale for Depression [25]; (6) drug safety through creatinine, liver transaminases, alkaline phosphatase, complete blood count, fasting glucose, thyroid stimulating hormone levels (TSH), total T4 or total thyroxin levels (T4), weight and cholesterol; (7) problems related to necessity, effectiveness, and security of the pharmacotherapy (NOMs to be identified and measured); (8) drug-related problems in drug therapy effectiveness, and safety; (9) the impact of side effects of antipsychotic drugs on health-related quality of life with a specific self-rated instrument: the ‘Tolerability and quality of Life’ (TOOL) questionnaire [26]; and (10) the patient’s satisfaction with the pharmaceutical care service measured through the patient satisfaction questionnaire on pharmaceutical care [27]. Control and intervention groups will be compared in terms of the proportion of changes from baseline to follow-up at 12 months. The information collected at 3, 6, and 9 months is part of the follow-up period of patients, and these data help to complement the secondary outcomes of the trial. Secondary outcomes will handled in terms of the proportion of changes from baseline to 12 months following.

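### Continuous secondary outcomes are compared by an undefined proportion of changes, with within-arm and unadjusted between-group tests left unranked and no baseline-adjusted comparison named as deciding

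*Protocol article*

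**What the plan says.** The secondary outcomes listed under Evaluation/assessment variables/measuring instruments include the Young, Hamilton and CGI-BP-M scales, SF-36, TOOL and laboratory values. For all of them: "Secondary outcomes will handled in terms of the proportion of changes from baseline to 12 months following". Biostatistical considerations repeats the metric for the comparison of the arms: "Control and intervention groups will be compared in terms of the proportion of changes from baseline to 12 months following". Neither section says what the phrase means for a continuous score.

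Biostatistical considerations then names these tests:

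- **Proportions.** The sentence opens with the between-group test, "The Pearson chi-square test (between study groups"), and continues with the within-arm one: "the McNemar test (within-group changes from baseline to follow-up at 12 months) will be used to compare proportions".
- **Means.** "The paired Student’s t-test (within-group changes from baseline to follow-up at 12 months) or the independent sample Student’s t-test (between study groups"). The two are joined by *or*, with no rule for choosing.
- **Outcomes in general.** "The Mann-Whitney test will be used to compare outcomes between groups".
- **Quality of life.** "For quality-of-life questionnaire the Student’s t test will be used if sample distribution proves to be normal", with the rank-sum test as the fallback.
- **Repeated measures.** Such an analysis is planned for depression and mania episodes, adherence and quality of life. Its terms are not given.

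The section closes with a single two-tailed P<0.05 rule for all comparisons. The Abstract names McNemar, chi-square and t tests, and no repeated-measures or adjusted analysis.

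**The concern.** Three things combine.

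1. **The metric is open.** It could mean percentage change per patient, or the share of patients who change. The second needs a threshold, which is not given, and it discards information on a continuous scale.

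2. **Within-arm tests carry the same significance label as between-group tests.** A significant change in the intervention arm beside a non-significant one in control could be reported as effectiveness, although it does not compare the arms. Both arms receive written and verbal education, and the Discussion says that the education and extra attention may benefit the usual-care patients. Patients also enter at discharge or outpatient referral, so regression to the mean is plausible. Change in both arms without any effect of the Dader Method is therefore a realistic case.

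3. **No between-group test that is named uses the baseline value as a covariate**, although every scale is measured at baseline. With no deciding analysis named, the choice among tests could be made after the results are seen.

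**Working it through.** The documents give no SD, correlation or expected change for any scale, so there is no figure of the plan's own to reproduce; the sample-size calculation concerns readmission. Inputs from the documents are 200 patients (Sample size calculation), equal allocation (Randomization), hence 100 per arm, and two-tailed 0.05 (Biostatistical considerations). The correlation r between baseline and month 12, and all effect sizes, are assumptions. SDs are taken as equal at both times.

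**Misleading within-arm result.** Let both arms change equally, with each within-arm test reaching significance with probability p. The chance that the intervention arm alone is significant is about p(1−p), which is largest at p = 0.5: 0.5 × 0.5 = 0.25.

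In score units, with r = 0.5 and 100 per arm, the SE of the mean change is √(2(1−0.5)/100) = 0.10 SD, and p = Φ(m/0.10 − 1.96) for a common improvement of m SD:

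| m (SD) | p per arm | intervention arm only |
|---|---|---|
| 0.1 | 0.17 | 14% |
| 0.2 | 0.52 | 25% |
| 0.3 | 0.85 | 13% |
| 0.4 | 0.98 | 2% |

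Simulation with 20,000 trials gave 24% at 0.2 SD and 13% at 0.3 SD. A between-group test of change in the same data rejected in 5.1% and 4.8%. By symmetry about half of a 5% two-sided error, 2.5%, would favour the intervention.

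**Precision.** Variance of the between-group difference, relative to the month-12 score alone:

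- follow-up score: 1
- change score: 2(1−r)
- ANCOVA: 1−r²

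ANCOVA relative to change is therefore (1−r²)/(2(1−r)) = (1+r)/2.

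| r | ANCOVA / change | ANCOVA / follow-up |
|---|---|---|
| 0.3 | 0.65 | 0.91 |
| 0.5 | 0.75 | 0.75 |
| 0.7 | 0.85 | 0.51 |
| 0.8 | 0.90 | 0.36 |

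For a difference of 0.4 SD with 100 per arm, power is Φ(0.4/√(2v/100) − 1.96), where v is the relative variance:

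| r | follow-up | change | ANCOVA |
|---|---|---|---|
| 0.3 | 81% | 67% | 84% |
| 0.5 | 81% | 81% | 90% |
| 0.7 | 81% | 96% | 98% |

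**If the metric means the share of patients who change.** Take a difference of 0.4 SD of change and a threshold midway between the arm means. The shares above it are Φ(0.2) = 0.58 and 0.42. With 100 per arm the two-proportion test has about 61% power, against 81% for a t test on the undivided change.

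**The case against.** The strongest reply is that between-group comparison is planned. Chi-square, Fisher, independent t, Mann-Whitney and rank-sum tests are all named between groups, and the McNemar sentence itself begins with a between-group chi-square. The repeated-measures analysis may contain baseline and a group-by-time contrast, and its terms may properly sit in an analysis plan that is not shown. An unadjusted t test is valid in a randomized trial. For quality of life, the rank-sum test is a stated fallback and not a rival to the t test. All of this stands. A reader might infer that within-arm tests replace between-group ones; the documents do not support that.

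Four other strong readings also fail:

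- *The metric divides by zero in patients without symptoms.* This requires the percentage-change reading. The nearby sentences on comparing proportions make the share of patients who change at least as natural.
- *The risk of a misleading result is 50%.* That counts trials in which either arm alone is significant. The harmful case is the intervention arm alone, at most 25%.
- *McNemar on hospitalization would be significant without any effect.* The documents give no baseline hospitalization rate, so no size can be attached to this.
- *Adjustment for adherence removes part of the effect.* The covariate list does include "having no insight, non-compliance to medication, lack of practical support from the family", but that model seeks factors related to the primary outcome, and nothing says that post-randomization values are used.

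The reply does not remove what the article fixes in its own words: an undefined metric, within-arm tests under the common significance rule, and a list of tests with none deciding.

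**Conclusion.** The point holds as a fault of definition and ranking in the continuous secondary outcomes. It does not show that between-group analysis is missing or that the planned between-group tests are invalid.

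The 25% is a ceiling. It assumes equal change in both arms, 50% power within each arm, and a report that leans on the within-arm results; at other sizes of change the risk is lower. The precision gain from using baseline is a variance reduction of 10 to 35% against change scores and 9 to 64% against follow-up scores, over an assumed r of 0.3 to 0.8. It cannot be narrowed from the documents, and it would be smaller or nil where the repeated-measures analysis already uses baseline. Regression to the mean in both arms is plausible, not certain. The change is worth making because it is almost free and removes a clear route to a false claim.

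**What to change.** - For each continuous scale, replace the proportion of changes with one deciding between-group analysis: a linear mixed model on months 3, 6, 9 and 12 with arm, visit, arm-by-visit and the baseline value as covariate, or ANCOVA at month 12. Report the adjusted month-12 difference with its 95% CI.
- For adherence as a binary outcome, use logistic regression adjusted for baseline adherence.
- Label the McNemar and paired t tests descriptive, and exclude them from the P<0.05 rule.
- As a minor clarification, state that covariates in any multivariable model that includes arm are baseline values.

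Baseline and three-monthly assessments are already planned, so no data collection changes. The cost is wording and slightly more analysis.
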